### Safety assessments

2.7

During the study period, subjects will be continuously monitored for frequency, severity, and aspect of events of special interests (ESIs). ESIs include paronychia, loss of appetite, diarrhea, stomatitis, cheilitis, rash, acne dermatitis, interstitial lung disease, and severe hepatopathy. The overall safety profile will be evaluated by using safety indicators such as the numbers of abnormal cases and adverse drug reactions, the frequency of significant abnormalities, as well as severities and aspects of abnormalities, physical examination findings, abnormal vital signs, clinical laboratory findings, and clinically significant changes in the ECOG PS scores. The treatment discontinuation rate and reason will be recorded.

In this clinical trial, the “Data and Safety Monitoring Board (DSMB)” will be operated as a safety protection measure for the test subjects. The board will meet every 6 months after the commencement of the study to evaluate the overall safety of clinical trials.

### Randomization and blinding

2.8

Random assignment will be performed using a computer-generated, blocked, random-allocation sequence with a 1:1 ratio. Each participant will be assigned to a group according to a pre-generated randomization table and an assigned randomized number. Each participant will be assigned to a treatment group, or the control group according to the allocation codes of the randomized assignment method, which will be prepared in advance. In this clinical trial, blinding is not performed.

### Sample size calculation

2.9

According to the paper, the Afatinib group’s starting dose maintenance rate is assumed to be 57.6 percent, while the Afatinib + HAD B1 group’s starting dose maintenance rate is assumed to be 80.0 percent. Furthermore, it is assumed that all patients will be recruited and monitored for at least 16 weeks. As a result, each group has 64 test subjects. With a 10% dropout rate, 71 people will be recruited for a total of 142 people.^[14]^

### Statistical analysis

2.10

#### Analysis of first outcome variables

2.10.1

The frequency and percentage of afatinib’s initial dose maintenance rate for afatinib and disease control rate (DCR) according to RECIST 1.1 up to 16 weeks relative to baseline will be presented, and the statistical significance of differences between groups will be analyzed using Chi-square test or Fisher’s effect test.

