### Inclusion criteria

2.3

Participants meeting the following criteria will be included:

1.Pathologically confirmed locally advanced or metastatic NSCLC (Stage IIIA-IV based on the eighth edition of the American Joint Commission on Cancer TNM staging system)^[9]^;2.Mutated EGFR and requiring first line afatinib therapy (in the judgment of the researcher);3.Disease measurable using Response Criteria for Clinical Trials of Cancer (RECIST) 1.1^[10]^;4.ECOG performance status score from 0 to 2^[11]^;5.Ability to take the drug orally (in the judgment of the researcher);6.Nineteen years of age or older;7.Willingness to sign a written consent to participate in this trial.

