### Outcome measures

2.6

**The primary measurement** is comparison of starting dose maintenance rate for afatinib and disease adjustment rate (DCR) at 16 weeks in accordance with RECIST 1.1 of Afatinib + HAD-B1 combined group and afatinib monotherapy group. The secondary outcomes are comparisons of the Progressive Free Survival (PFS) determined by RESIST 1.1, overall survival rate (OS), objective response rate (ORR), tumor size reduction, time to progression (TTP), HRQoL, and tumor markers (CEA, NSE) between the 2 groups. The PFS, ORR, DCR, and TTP are evaluated on the basis of RECIST 1.1 criteria.^[10]^ This clinical trial will explore whether the prognosis varies according to cold-heat pattern in Korean medicine. Cold-heat pattern identification will be evaluated using the usual symptom-based CHPIQ, which has been recognized for its reliability and validity.^[13]^

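### The unadjusted primary tests are valid, but adjusting both for ECOG status and stage, and not using Fisher's test for dose maintenance, would be a cheap improvement

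*Protocol article*

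**What the plan says.** Section 2.6 of the protocol article sets two binary primary outcomes: "comparison of starting dose maintenance rate for afatinib and disease adjustment rate (DCR) at 16 weeks". Section 2.10.1 gives one sentence of method for both: "differences between groups will be analyzed using Chi-square test or Fisher’s effect test" (evidently Fisher's exact test). It names no covariate or stratum and gives no rule for choosing between the two tests.

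Section 2.3 admits patients with "ECOG performance status score from 0 to 2" and with stage IIIA to IV disease. Section 2.8 describes allocation as a "computer-generated, blocked, random-allocation sequence with a 1:1 ratio" and names no stratification factor.

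Section 2.9 bases the sample size on dose maintenance alone. The control arm's "starting dose maintenance rate is assumed to be 57.6 percent" and the combination arm's "starting dose maintenance rate is assumed to be 80.0 percent", leading to 64 per group and, after dropout, 71 per group. Alpha, sidedness, power and any DCR rates are not given.

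**The concern.** ECOG status and stage are recorded before randomisation and vary widely in the admitted population. If either one predicts keeping the starting dose or disease control at 16 weeks, two things follow.

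- A chance imbalance between arms of this size shifts the observed difference, and an unadjusted two-by-two test cannot correct the shift.
- The unadjusted test may have less power than one that uses the factors.

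Nothing stated in the randomisation section limits such an imbalance by design.

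The same sentence leaves Fisher's test available for dose maintenance. If it were used there, power would be lost whether or not any factor is prognostic.

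**Working it through.** **1. The plan's own figure.** Inputs from section 2.9 are 0.576 and 0.80. Two-sided alpha 0.05 and 80% power are assumed. The unpooled formula gives

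n = (1.960 + 0.842)² × (0.576×0.424 + 0.80×0.20) / 0.224² = 7.849 × 0.4042 / 0.05018 = 63.2, rounded up to 64 per group.

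This matches the stated 64. The sample size therefore rests on a plain comparison of two proportions, the same basis as the unadjusted chi-square test.

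**2. Chi-square against Fisher for dose maintenance.** The pooled rate is (57.6 + 80.0)/2 = 68.8%. The smallest expected count at 64 per arm is 64 × 0.312 = 20.0, far above 5. Exact results, summing over all outcome tables:

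| | Chi-square | Fisher |
|---|---|---|
| Power, 64 per arm | 79.5% | 73.0% |
| Power, 71 per arm | 83.7% | 78.3% |
| Type I error at 68.8%, 64 per arm | 5.1% | 3.1% |

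The difference is 6.5 points at 64 per arm and 5.4 at 71. It needs no assumption about prognosis.

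**3. Size of a chance imbalance.** Assume simple randomisation, 64 per arm, 15% ECOG 2 and 80% stage IV. The 95% range is 1.96 × √(2p(1−p)/64):

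- ECOG 2: 1.96 × √(2×0.15×0.85/64) = ±12.4 points.
- Stage IV: 1.96 × √(2×0.80×0.20/64) = ±13.9 points.

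To turn this into a shift, take 68.8% (odds 2.205) as the rate without the factor.

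- Odds ratio 2: odds 1.103, rate 52.4%, a gap of 16.4 points. The shift is 0.124 × 16.4 = 2.0 points for ECOG and 0.139 × 16.4 = 2.3 for stage.
- Odds ratio 3: odds 0.735, rate 42.4%, a gap of 26.4 points. The shift is 0.124 × 26.4 = 3.3 points for ECOG and 0.139 × 26.4 = 3.7 for stage.

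The planned difference is 22.4 points.

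**4. Power with and without adjustment.** Simulation used 4,000 trials per setting and 64 per arm, with marginal rates held at 57.6% and 80.0% and the same odds ratio for each factor. The adjusted tests were Cochran-Mantel-Haenszel (CMH) by ECOG × stage and logistic regression (Wald test) on both factors.

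| ECOG 2 / stage IV | Odds ratio | Chi-square | CMH | Logistic | Change (points) |
|---|---|---|---|---|---|
| 15% / 80% | 1 | 80.8% | 79.1% | 79.6% | −1.7 to −1.2 |
| 15% / 80% | 1.5 | 79.2% | 78.0% | 78.4% | −1.2 to −0.8 |
| 15% / 80% | 2 | 79.3% | 79.4% | 80.0% | +0.1 to +0.7 |
| 15% / 80% | 3 | 79.3% | 80.9% | 81.3% | +1.6 to +2.0 |
| 15% / 80% | 5 | 79.4% | 82.9% | 83.2% | +3.5 to +3.8 |
| 30% / 60% | 2 | 78.9% | 79.8% | 80.4% | +0.9 to +1.5 |
| 30% / 60% | 3 | 78.5% | 81.1% | 81.2% | +2.6 to +2.7 |
| 30% / 60% | 5 | 79.3% | 85.8% | 86.2% | +6.5 to +6.9 |

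Under the null (15% / 80%), rejection was 5.0 to 5.7% for chi-square, 4.8 to 5.4% for CMH and 5.0 to 5.6% for logistic regression. Each power figure has a simulation standard error of √(0.8×0.2/4000) = 0.6 points.

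A separate simulation at 71 per arm (20% ECOG 2, 80% stage IV) gave 84.7% to 84.2% with no prognostic effect, a loss of 0.5 points. It gave 83.9% to 85.3% with ECOG and stage odds ratios of 0.33 and 0.5, and 83.4% to 86.9% with 0.2 and 0.4.

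**The case against.** The strongest reply is that the plan contains no error here. A two-by-two test is valid under randomisation, keeps its type I error and agrees with the sample size calculation. All of that stands. A reader might infer that the plan as written gives power away. The document does not support this, because it states neither the prevalence of ECOG 2 and stage IV nor how strongly either predicts the two outcomes. With weak prognosis, adjustment costs a little power.

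Second, offering chi-square or Fisher is common shorthand for using Fisher when counts are small. On that convention chi-square would be used for dose maintenance and the 6.5-point loss would not arise. The option can also have a use for DCR. The introduction speaks of high disease control rates, and at 64 per arm the expected number without control falls below 5 once the pooled rate exceeds 1 − 5/64 = 92.2%. This stands, so the loss is what Fisher would cost if used and not a forecast.

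Third, a condensed article may leave covariates and the rule for choosing a test to the full protocol or analysis plan. That holds for supportive analyses. The primary test itself, however, is positively stated here, and naming a different one changes stated method.

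A reader might also argue that ignoring centre makes the test conservative. That needs blocks generated within centre, which the article does not state, so no such claim is made.

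**Conclusion.** The point holds as a modest improvement in efficiency and precision. The unadjusted chi-square test remains a valid primary analysis.

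An imbalance at the edge of its 95% range would move the observed difference by about 2 points per factor at odds ratio 2 and 3 to 4 points at odds ratio 3. Depending on prognostic strength, adjustment changes power by anything from a loss of 1.7 points to a gain of about 7. Gains above 3 points need strong prognostic factors, with odds ratios near 5. These figures rest on assumed prevalences and odds ratios.

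The cost of Fisher's test for dose maintenance rests only on the plan's own rates and an assumed two-sided 5% level.

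**What to change.** In section 2.10.1 and the analysis plan, name one primary test per endpoint: a logistic-model score test of treatment (or a CMH test) adjusted for ECOG status (0–1 vs 2) and stage (III vs IV). Report the standardised risk difference with its 95% confidence interval, and keep the unadjusted Pearson chi-square test as supportive.

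Remove Fisher's test for dose maintenance. For DCR, keep an exact test only as a fallback if expected counts fall below 5, and write that rule down. Leave centre out of the analysis unless the full protocol shows that blocks are generated within centre.

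The cost is wording, with no new data and no new patients. The statistical price is about 0.5 to 1.7 points of power if the two factors turn out to be weak or not prognostic.

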#### Analysis of second outcome variables

2.10.2

We will compare and evaluate the following between the treatment group and the control group at each time point from the baseline (0 week) to 16 weeks: Progressive survival period (PFS), the time to progression (TTP), and the overall survival rate (OS) present descriptive statistics (number of subjects tested, mean, standard deviation, median, minimum and maximum) and compare statistical significance through Kaplan–Meier analysis. The frequency and percentage of changes in objective response rates (ORR), QOL (EORTC QLQ-C30, EORTC QLQ-LC13, EQ-5D) according to RECIST 1.1 will be presented, and the statistical significance of differences between groups will be analyzed using Chi-square test or Fisher’s exact test.

The reduction of tumor size and tumor markers present descriptive statistics by dose group (number of subjects, mean, standard deviation, median, minimum, and maximum), and statistical significance of differences between groups is to be analyzed by two-sample-test or Wilcoxon signified rank test.

The statistical significance of the variation within each group is tested as either a paired *t*-test or a Wilcoxon signed rank test.

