### Trial design

2.1

This clinical trial is a randomized, multi-centre, open-label study that aims to compare the safety and efficacy between afatinib monotherapy and combination therapy with afatinib plus HAD-B1 for the treatment of patients with locally advanced or metastatic EGFR-mutation-positive NSCLC. Participants will be randomized using a ratio of 1:1 into a treatment group (afatinib 20–40 mg/day plus HAD-B1 2 tablets [972 mg/day]) and a control group (afatinib 20–40 mg/day monotherapy) and will be treated for 16 weeks. As treatment continues, follow-up visits will be scheduled at Day 1, week 2, 4, 8, and 16. Physical examination, vital signs, ECOGPS, clinical laboratory examination, tumor marker examination, imaging diagnosis and tumor evaluation, health-related quality of life survey, combined drug confirmation, and abnormal case evaluation are all performed during each visit. Furthermore, for cold-heat pattern identification and genetic search studies, PMRA chip tests and cold-heat pattern identification surveys are performed prior to randomization.

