In light of the above, this prospective, multicenter, randomized, controlled trial will verify the efficacy and safety of a combination therapy of afatinib plus HAD-B1 in treating patients with locally advanced or metastatic NSCLC. At the same time, this trial may provide clinical evidence supporting integrative medicine and may propose synergistic effects of treating such patients with this combination therapy.

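### Section 2.10.2 tests the repeatedly measured secondary outcomes between arms at every time point, and tests change within each arm, without naming a deciding time point

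*Protocol article*

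**What the plan says.** Section 2.10.2 of the protocol article opens with a timing rule for the secondary outcomes: "We will compare and evaluate the following between the treatment group and the control group at each time point from the baseline (0 week) to" week 16. It then assigns tests: Kaplan–Meier comparison for PFS, TTP and OS; chi-square or Fisher for ORR and for quality of life, given as "QOL (EORTC QLQ-C30, EORTC QLQ-LC13, EQ-5D"; and a two-sample or Wilcoxon test for tumour size and tumour markers. It closes with a further rule: "The statistical significance of the variation within each group is tested as either a paired *t*-test or a Wilcoxon signed rank test".

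Section 2.1 supplies the time points: "follow-up visits will be scheduled at Day 1, week 2, 4, 8, and 16". The same section says that tumour evaluation, tumour markers and quality of life are assessed at each visit. Section 2.6 lists, besides PFS, "overall survival rate (OS), objective response rate (ORR), tumor size reduction, time to progression (TTP), HRQoL, and tumor markers (CEA, NSE".

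Elsewhere the article does fix a time point. The primary outcomes in section 2.6 and the changes in laboratory, vital-sign and ECG results in section 2.11 are tied to 16 weeks.

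**The concern.** The timing rule gives each repeatedly measured secondary up to four between-arm p-values, with nothing to say which one answers the question. The trial is open-label, so the visit that is reported as positive could be chosen once the data are known. The usual 5% no longer describes the chance of a false positive, either for one endpoint across its visits or for the set.

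The within-arm tests are a separate problem. Both arms receive afatinib, so tumour size and markers may well change in both. A significant change in the HAD-B1 arm therefore cannot be credited to HAD-B1. If one arm reaches significance and the other does not, the pair of results is easily read as a difference between arms that was never tested.

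**Working it through.** **Inputs**
- From section 2.1: post-baseline visits at weeks 2, 4, 8 and 16, so 4 (Day 1 is not counted).
- From sections 2.6 and 2.10.2: seven repeatable outcomes (ORR, QLQ-C30, QLQ-LC13, EQ-5D, tumour size, CEA, NSE) and three that a Kaplan–Meier comparison naturally tests once (PFS, TTP, OS).
- From section 2.9: 64 per arm before dropout.
- Assumed: two-sided 5% per test (the article states no alpha), the correlations between tests, and the standardised within-arm changes.

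**The plan's own figure.** The article gives no error rate for the secondaries. Its 64 per arm can be reproduced: (1.960 + 0.842)² × (0.576 × 0.424 + 0.80 × 0.20) / (0.80 − 0.576)² = 63.2, rounded up to 64, at two-sided 5% and 80% power. The 5% assumption is thus consistent with the sample size, though the article does not confirm it.

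**Number of tests.** 7 × 4 + 3 = 31. Questionnaire subscales are left out because the article does not say how many would be tested.

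**Independent tests.** Any difference: 1 − 0.95³¹ = 80%. In favour of HAD-B1 only (2.5% per test): 1 − 0.975³¹ = 54%.

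**Correlated tests.** The tests are not independent, so each statistic was modelled as z = √a·G + √(b − a)·B + √(1 − b)·e. Here G is shared by all tests, B is shared within an outcome and e is specific to a visit. The correlation between outcomes is a and that between visits of one outcome is b; with a = b it is one common correlation. The chance of any significant difference is 1 − P(all |z| < 1.96), and of a favourable one 1 − P(all z < 1.96).

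| 31 tests: correlation | Any difference | Favouring HAD-B1 |
|---|---|---|
| common 0 | 80% | 54% |
| common 0.3 | 67% | 36% |
| common 0.5 | 51% | 26% |
| common 0.8 | 26% | 13% |
| visits 0.5, outcomes 0.2 | 69% | 38% |
| visits 0.7, outcomes 0.2 | 64% | 35% |
| visits 0.7, outcomes 0.5 | 48% | 24% |

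**One endpoint at four visits.** Any difference: 17%, 16%, 13% and 11% at correlation 0.3, 0.5, 0.7 and 0.8.

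**Ten outcomes tested once each.** Any difference: 40%, 29% and 17% at correlation 0, 0.5 and 0.8.

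**Within-arm tests.** Let both arms have the same true standardised change d, and let p be the power of a paired t-test with 64 patients. Exactly one arm is significant with probability 2p(1 − p).

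| d | p | Exactly one arm significant |
|---|---|---|
| 0.2 | 0.35 | 46% |
| 0.25 | 0.50 | 50% |
| 0.3 | 0.66 | 45% |
| 0.5 | 0.976 | 5% |
| 0.8 | about 1 | near 0 |

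By symmetry, in half of these cases the significant arm is the HAD-B1 arm.

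**The case against.** The strongest reply is that these are secondary outcomes, labelled as such, in a journal article that condenses a fuller protocol. Testing supportive outcomes without adjustment is common, and a testing order or alpha allocation is usually left to the full protocol or SAP. That part stands: the absence of a hierarchy here is no finding. What it does not answer is the timing rule, which the article states outright and which a SAP must either follow or contradict.

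Three stronger readings are tempting and are not supported.
- A reader might infer that every secondary is tested at each visit and within each arm. Taken literally, the opening sentence covers all of them, but Kaplan–Meier comparisons of PFS, TTP and OS are naturally one each. Paired tests fit only change scores, such as tumour size, markers and perhaps quality-of-life scores.
- A reader might infer that a trial with no effect would more likely than not show a secondary benefit. A benefit needs the favourable direction, and that chance passes one half only close to independence. Repeated visits and overlapping outcomes (PFS with TTP, tumour size with ORR) make independence implausible.
- A reader might tie the Discussion's statement that the trial "will verify the efficacy and safety of a combination therapy of afatinib plus HAD-B1" to the secondaries. It is a general remark about the trial and attaches no confirmatory claim to any of them.

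It is also fair to say that the 45–50% within-arm discordance belongs to small true changes. If afatinib produces a large change in both arms, discordance all but disappears. Nor does the article say that within-arm p-values will serve as evidence of benefit. They still cannot inform the comparison of arms, whatever d is.

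**Conclusion.** The point holds for the repeatedly measured secondaries. Section 2.10.2 fixes between-arm significance tests at each time point with no deciding visit, and adds within-arm tests that do not compare the arms.

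Under no effect, the chance of at least one nominally significant between-arm difference is roughly 48–69% with moderate correlation (26–80% for a common correlation of 0.8 to 0). In favour of HAD-B1 it is about 24–38% (13–54%), against 2.5% for a single test. For one endpoint over four visits it is 11–17% instead of 5%. With equal true change in both arms, within-arm tests would disagree in 45–50% of trials for a standardised change of 0.2–0.3, in 5% at 0.5 and almost never at 0.8.

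These sizes rest on the assumed 5% level, the count of 31 and the assumed correlations and effect sizes. The lack of a deciding time point is read directly from the text and depends on none of them.

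**What to change.** In section 2.10.2:
- Replace the each-time-point rule with one named between-arm contrast for each repeatedly measured secondary. Week 16 would match the primary outcomes. For ORR, state one response measure.
- State one overall comparison each for PFS, TTP and OS.
- Report weeks 2, 4 and 8 descriptively, without significance tests.
- Report within-arm change as an estimate with a confidence interval and drop its p-value.
- Describe the secondaries as supportive. This is still needed after the other changes, because ten outcomes tested once each leave a 17–40% chance of some nominally significant difference.

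The cost is wording in this section and a matching analysis plan, with no extra patients or data. The small downside is that early-visit differences and within-arm changes can no longer be reported as statistically significant.

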### Recruitment and consent

2.2

A total of 142 EGFR-mutation-positive patients with locally advanced or metastatic NSCLC patients who need afatinib therapy will be recruited at 8 centers. All subjects will undergo standardized interviews and receive clinical research information on the trial. Written informed consent will be obtained from each subject. The purpose, procedure, and potential benefits and risks of the study will be thoroughly explained to the subjects. The subjects can withdraw from the study at any time without consequence. The trial covers the period from October 31, 2020 to December 2, 2022 (anticipated), including the enrollment and follow-up periods (Fig. 1).

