### Interventions

2.5

Patients in the treatment group will receive of 1 capsule/day of afatinib (20–40 mg/day orally) plus 2 HAD-B1 tablets (972 mg/day, bid orally) while those in the control group will only receive 1 capsule/day of afatinib (20–40 mg/day orally), which may be changed based on the medical judgment of the investigator. The investigator may extend the duration of the drug’s administration. The HAD-B1 tablets used in this trial will be purchased from the Hanpoong Pharmaceutical Co., Ltd. (Seoul, Korea). HAD-B1 is a medical substance containing *Panax ginseng C.A.* (640 mg), *Panax notoginseng Radix* (839 mg), *Cordyceps militaris* (640 mg), and *Boswellia carterii BIRDWOOD* (480 mg) as raw material medicines. In the toxicity assessment of HAD-B1 orally administered to rats for 13 consecutive weeks, the no-observed-adverse-effect-level (NOAEL) for HAD-B1 was determined as 2000 mg/kg/day. The human equivalent dose (HED) was calculated as approximately 320 mg/kg/day, which was about 19 g/day for a person of 60 kg.^[12]^ The dose of HAD-B1 in this clinical trial is approximately 1/20 of that. In the treatment group, when afatinib is removed, HAD-B1 is also removed; however, when afatinib is reduced, HAD-B1 is not reduced.

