## Discussion

3

Afatinib is an ErbB family of blockers that inhibit the EGFR signaling pathway by irreversibly fastening to the ATP domain of ErbB family kinase domains. The efficacy and safety of afatinib in the management of patients with advanced-stage NSCLC harboring EGFR mutations were evaluated in a comprehensive clinical trial program (LUX-Lung) that included several, randomized studies of afatinib as a first-, second-, or third-line treatment for patients with lung adenocarcinomas.^[15–21]^ Despite initial positive responses to EGFR-TKIs, an acquired resistance inevitably leads to disease progression in most patients within 9 to 13 months, and major adverse events grade 3 or higher, including diarrhea, rash or acne, and stomatitis or mucositis, occurred.^[21–23]^

Interest in complementary and alternative medicines for the treatment of patients with cancer because of their synergistic effects when combined with western medicine is growing in Korea. HAD-B1 has shown a potential synergetic therapeutic effect in conjunction with western medicine in vitro or in vivo studies.^[24–27]^ One multicenter, randomized, controlled trial reported that EGFR-TKI with Chinese herbal medicine improved the PFS (13.50 months; 95% CI, 11.20–16.46 months) when compared with TKI alone (10.94 months; 95% CI, 8.97–12.45 months; hazard ratio, 0.68; 95% CI, 0.51–0.90; *P* = .0064) in patients with EGFR mutation-positive NSCLC plus less common adverse events.^[28]^ The extended PFS and the overall survival (OS) in cancer patients using traditional medicine in conjunction with EGFR-TKIs have been demonstrated in various clinical studies.^[28–30]^ However, those studies had either been retrospective or had small samples; moreover, the influence of the cold-heat pattern was never studied. The cold-heat pattern is 1 diagnostic method frequently used in Korean medicine. In this clinical trial, in order to find a customized precision medicine system for the treatment of patients with lung cancer, we will identify the cold-heat patterns of the patients by using an objective and reliable cold-heat questionnaire to determine whether the prognosis varies depending on the cold-heat pattern.

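### PFS, TTP and OS are to be summarised by mean, SD, minimum and maximum, which are not valid for censored times, and the only stated window (16 weeks) would leave most patients censored

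*Protocol article*

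**What the plan says.** Section 2.10.2 (Analysis of second outcome variables) opens by saying that the groups will be compared "at each time point from the baseline (0 week) to 16 weeks", and lists PFS, TTP and OS directly under that window. For these three endpoints it will "present descriptive statistics (number of subjects tested, mean, standard deviation, median, minimum and maximum) and compare statistical significance through Kaplan–Meier analysis".

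Other sections bear on the length of observation:

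- Section 2.1 (Trial design) sets 16 weeks of treatment, and "follow-up visits will be scheduled at Day 1, week 2, 4, 8, and 16".
- Section 2.9 (Sample size calculation) assumes that "all patients will be recruited and monitored for at least 16 weeks".
- Section 2.5 (Interventions) lets the investigator prolong treatment.
- Section 2.2 (Recruitment and consent) says: "The trial covers the period from October 31, 2020 to December 2, 2022 (anticipated), including the enrollment and follow-up periods".

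None of these sets a later cutoff for PFS, TTP or OS. The Discussion (section 3) says of EGFR-TKI treatment that "an acquired resistance inevitably leads to disease progression in most patients within 9 to 13 months". It also cites a randomised trial of EGFR-TKI with Chinese herbal medicine, with median PFS of 13.50 against 10.94 months and a hazard ratio of 0.68.

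**The concern.** The list of descriptive statistics is the one that the next paragraph of section 2.10.2 applies to tumour size and tumour markers, which are not censored times. For a patient who has not progressed at the end of observation, the time to progression is known only to exceed the last observed time. An ordinary mean or SD must then either treat that time as an event time or leave the patient out, and both give a biased answer. The minimum and maximum have the same difficulty: if observation stops at week 16, the maximum is about 16 weeks in each arm by design.

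The short window makes this worse. When most patients are censored at the same time, naive means are pulled to that time in both arms. A table showing almost equal mean PFS could be read as evidence that HAD-B1 does not delay acquired resistance, which is the reason the Introduction gives for seeking new combinations.

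**Working it through.** **The plan's own figure.** The article gives no event count or power for PFS, TTP or OS. Its one sample-size figure, 64 per group, concerns starting dose maintenance (57.6% against 80.0%). With two-sided alpha 0.05 and 80% power (assumed, as the article states neither), the unpooled formula gives (1.96 + 0.842)² × (0.576 × 0.424 + 0.80 × 0.20) / 0.224² = 63.2, rounded up to 64. It reproduces and is not touched by this point.

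**Inputs.**
- Window w = 16 weeks = 112 / 30.44 days = 3.68 months (section 2.10.2).
- Control median m = 9, 10.94 or 13 months (section 3). The article says most patients progress within 9 to 13 months; using that range as a median is an assumption.
- Hazard ratio 0.68, from the cited herbal-medicine trial (section 3). That it applies here is an assumption.
- 71 patients per arm (section 2.9), exponential PFS, no loss to follow-up (the last two are assumptions).

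**Share progressed by week 16.** Control: p = 1 − 0.5^(w/m). Combination: the same with median m/0.68.

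| Control median (months) | p control | p combination | Events, 71 + 71 | Censored |
|---|---|---|---|---|
| 9 | 24.7% | 17.5% | 17.5 + 12.4 = 30.0 | 78.9% |
| 10.94 | 20.8% | 14.7% | 14.8 + 10.4 = 25.2 | 82.3% |
| 13 | 17.8% | 12.5% | 12.6 + 8.9 = 21.5 | 84.8% |

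So about 22–30 PFS events are expected among 142 patients, and 79–85% are censored. No arm comes near 50% progressed, so the Kaplan–Meier median is not reached. A raw median of recorded times would be 16 weeks in both arms. Every death is a PFS event, so OS cannot have more events than PFS.

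**Naive mean if censored times are averaged as recorded.** The true exponential mean is μ = median / ln 2. The mean of times cut at w is μ × p.

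| Control median (months) | True means, control / combination | Cut at week 16, control / combination | Difference: true → cut |
|---|---|---|---|
| 9 | 12.98 / 19.09 | 3.20 / 3.35 | 6.1 → 0.14 |
| 10.94 | 15.78 / 23.21 | 3.28 / 3.40 | 7.4 → 0.12 |
| 13 | 18.76 / 27.58 | 3.34 / 3.44 | 8.8 → 0.10 |

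Using the two cited medians directly (10.94 and 13.50 months), true means of 15.8 and 19.5 become 3.28 and 3.35 months. Averaging only the patients who progressed, μ − w(1 − p)/p, gives 1.77 and 1.78 months. Either way the difference nearly vanishes.

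**What the window means for the valid comparison.** By Schoenfeld's formula, power is Φ(√(d/4) × |ln 0.68| − 1.96). With d = 21.5 to 30.0 events this is 14% to 18%. For 80% power, d = 4 × (1.96 + 0.842)² / (ln 0.68)² ≈ 211 events, more than the 142 patients. If patients were followed to December 2022 (about 25 months, with uniform accrual ending 16 weeks before the close, an assumption), about 64–81 events would be expected, with power of 34–41%. Longer follow-up would improve the estimate but would not make PFS a powered endpoint.

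**The case against.** The strongest reply is that section 2.10.2 separates description from comparison. Significance is to be assessed through Kaplan–Meier analysis, which handles censoring, and no test of raw means is planned for these endpoints. This stands. A reader might infer that the whole PFS and OS comparison is invalid, and the document does not support that. Nor does it say that progression-free patients will be counted as events, and the listed median could be the Kaplan–Meier median. But no such reading rescues mean, SD, minimum and maximum. These are stated choices, not details left out, and an analysis plan that followed the sentence would carry them forward.

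Kaplan–Meier is an estimator, and the article names no log-rank test, hazard ratio or censoring rule. A reader might take that as a fault, but a condensed article may leave such detail to the full protocol or analysis plan.

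A reader might also infer that observation certainly stops at week 16. The text does not settle this. The lead-in covers the secondary outcomes generally and suits visit-based measures better, while sections 2.2, 2.5 and 2.9 leave room for longer observation. Still, 16 weeks is the only analysis window stated and the last scheduled visit.

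Finally, PFS is secondary, so low power is not in itself a defect, and longer follow-up would not cure it. That also stands.

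**Conclusion.** The point holds in a limited form. Four of the planned summary statistics are invalid for PFS, TTP and OS, whatever the length of follow-up. Under the only stated window, about 79–85% of patients would be censored, the median would not be reached, and naive mean PFS would differ by only 0.10–0.14 months where the true means differ by 6–9 months. These sizes rest on exponential PFS, a control median of 9–13 months, a hazard ratio of 0.68 and no loss to follow-up. The invalidity of the summaries does not depend on them.

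Severity is moderate: the correction is specific and almost free, but the endpoints are secondary and the planned comparison method is sound.

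**What to change.** 1. In section 2.10.2, delete mean, SD, minimum and maximum for PFS, TTP and OS. Report Kaplan–Meier medians (or 'not reached') and week-16 PFS, TTP and OS rates with 95% CI. Compare the groups by log-rank test and give a Cox hazard ratio with CI. This costs only wording.
2. Reconcile the baseline-to-week-16 window with the follow-up period in section 2.2 and the minimum of 16 weeks in section 2.9. If follow-up beyond week 16 is already collected, analyse all of it and state the cutoff; this needs no new data.
3. If it is not collected, label the results as 16-week rates that are descriptive and not evidence on delayed resistance. This too costs only wording.

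Adding progression and survival data collection after week 16 would be a larger step. It changes data collection, and in an open-label trial irregular assessment timing could bias the dating of progression. It is a choice for the sponsor and is not needed to correct the error.
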